## Abstract

**Background:**

Stimulant use disorders (StimUDs), including cocaine and methamphetamine use disorders, remain a major public health concern in the United States with no US Food and Drug Administration (FDA)–approved pharmacological treatments. The early recovery period following stimulant use is marked by sleep disturbances, heightened stress reactivity, and dysregulated reward processing, contributing to high rates of resumption of use. Evidence from animal and human studies supports the orexin neuropeptide system as a promising therapeutic target for minimizing these disruptive mechanisms. Suvorexant, an FDA-approved dual orexin receptor antagonist for insomnia, has previously been shown to improve sleep, reduce stress, and attenuate craving in the first-in-human study with non–treatment-seeking individuals with cocaine use disorder.

**Objective:**

The primary objective of this randomized open-label clinical trial is to evaluate the effects of suvorexant on sleep, stress, reward processing, and craving during early abstinence in treatment-seeking individuals with StimUD. This proof-of-concept trial represents the first mechanistic evaluation of suvorexant in a residential sample of individuals with StimUD.

**Methods:**

A total of 40 participants, recruited from a residential treatment facility, will be randomized (1:1) to either 7 days of nightly suvorexant (10 mg) or treatment as usual. Participants’ sleep will be monitored using an activity tracker watch, and they will complete a sleep diary each night to confirm bedtimes and wake-up times. Participants in the suvorexant group will receive the study medication for 7 nights. On premedication and postmedication study days, participants will be transported to the Center for Neurobehavioral Research on Addiction to complete the study sessions. At both study sessions, participants will complete self-report and safety measures (safety measures for the suvorexant group only) followed by administration of a stress reactivity test and an electroencephalographic assessment.

**Results:**

The study was funded in January 2025 and is currently ongoing. We began enrollment of the first participant prior to funding in July 2024. At the time of manuscript submission (September 2025), a total of 8 participants had been enrolled in the study toward the planned enrollment of 40 participants. This study is expected to conclude in January 2027.

**Conclusions:**

Findings from this study will provide initial evidence for the mechanisms involved in suvorexant for StimUD, with the long-term goal of repurposing orexin-based therapy to regulate neurobehavioral mechanisms and inform future medication development for StimUD.

## Introduction

Stimulant use disorders (StimUDs), including cocaine and methamphetamine use disorders, represent a growing public health crisis in the United States. Unlike opioid use disorder, for which multiple pharmacotherapies exist, StimUDs remain without a US Food and Drug Administration (FDA)–approved medication, posing a significant challenge for clinical management. Historically, pharmacological interventions have targeted monoaminergic systems—particularly dopaminergic pathways—with limited efficacy [1]. This therapeutic gap underscores the urgent need for novel, mechanism-based treatments that address the neurobiological underpinnings of stimulant addiction and withdrawal.

One promising target is the orexin (hypocretin) system, a neuropeptide network originating in the lateral hypothalamus that plays a central role in regulating arousal, stress, and reward processing. Converging evidence from preclinical and translational studies implicates orexin signaling in the maintenance of drug-seeking behavior, particularly under conditions of heightened stress or disrupted sleep [2]. Of particular relevance to early abstinence is the role of orexin in sleep-wake regulation. Sleep disturbances are a hallmark of stimulant withdrawal and are strongly predictive of resumption of use [3]. Therefore, pharmacological modulation of orexin receptors may offer a dual mechanism of action—ameliorating sleep disruption while attenuating drug-motivated behavior.

Dual orexin receptor antagonists, such as suvorexant, have demonstrated efficacy in improving sleep architecture and reducing hyperarousal in individuals with insomnia. In a recent proof-of-concept study, suvorexant was shown to improve sleep quality, reduce stress, and attenuate craving in non–treatment-seeking individuals with cocaine use disorder [4]. Building on these findings, this study aims to evaluate the effects of suvorexant during early withdrawal in treatment-seeking individuals with StimUD, including those using both cocaine and methamphetamine, as they transition into residential addiction treatment.

To extend the mechanistic understanding of suvorexant’s effects, we incorporate electroencephalography (EEG) measures of brain function. Two neural markers are of particular interest. First, resting-state alpha power (8‐13 Hz), typically observed over posterior scalp regions during relaxed wakefulness, is sensitive to sleep pressure and may serve as an objective index of daytime neural deactivation [5]. Preliminary data from our group suggest that increased alpha power is associated with poorer subjective sleep quality in people who use stimulants. Second, the reward positivity (RewP) component—an event-related potential elicited by positive prediction errors—indexes reward sensitivity and is often blunted in individuals with substance use disorders [6]. Given the orexin system’s role in (1) modulating mesolimbic dopamine pathways and (2) normalizing sleep architecture, suvorexant may enhance neural responsiveness to nondrug stimuli (potentially both cues and rewards), thereby supporting recovery-related motivational processes.

The primary objective of this translational study is to evaluate the effects of suvorexant on sleep during early abstinence from stimulants—a critical window in which effective withdrawal management may reduce the risk of return to stimulant use. The secondary objective is to examine whether suvorexant will also improve reward processing and reduce stress and craving during early abstinence. By integrating behavioral, subjective, and neurophysiological measures, this investigation represents the first mechanism-focused clinical evaluation of orexin antagonism in StimUD. We hypothesize that suvorexant, relative to treatment as usual (TAU), will improve sleep outcomes during early abstinence (aim 1). We also hypothesize that the secondary outcomes (EEG resting alpha power, acute stress reactivity, non–drug-reward processing, and drug demand) will improve from pretreatment to posttreatment in the suvorexant group compared with the TAU group (aim 2). Finally, we will examine treatment engagement and the effects of the treatment group (suvorexant vs TAU) on posttreatment (days 13‐30) residential program length of stay and completion rates (aim 3). We hypothesize that participants in the suvorexant group, compared with the TAU group, will demonstrate longer posttreatment lengths of stay and higher residential program completion rates.

## Methods

### Study Design

We will use an open-label, randomized 2-group design. Participants (n=40) will be randomized to receive 7 days of suvorexant (10 mg) or TAU, consisting of supportive care and symptomatic medication. Figure 1 outlines the schedule of events. Informed consent, eligibility criteria, and baseline sleep data (via actigraphy) will be assessed on day 0 of the study via telephone or video call. Day 0 will ideally occur around 4 days (but within the first week) following admission to the residential program. On day 1 and day 8, participants will be transported to the outpatient treatment research clinic at the Center for Neurobehavioral Research on Addiction (CNRA) to complete the study sessions. At each study session, participants will complete self-report and safety measures (safety measures for the suvorexant group only) followed by administration of the stress reactivity test and then the EEG assessment. Details regarding each of these procedures are provided in subsequent sections. Participants in the suvorexant group will begin receiving the study medication, administered by residential nurses, from day 1 up until day 8 (ie, nights 1‐7). All participants will remain in the residential program until either regular discharge at approximately 30 days (“successful completion”) or early departure (eg, patient-directed discharge or leaving against medical advice). This design captures the critical first 2 weeks of stimulant withdrawal, when sleep disruptions and other withdrawal-related symptoms are typically most pronounced [7].

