**Figure 1. F1:**
[figure not shown]
Study flow diagram. Consent and randomization will occur virtually. Laboratory visits will occur at the Center for Neurobehavioral Research on Addiction. All other activities will occur at the inpatient facilities. NSF: National Sleep Foundation; TAU: treatment as usual.

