There are several strengths and seminal innovations to the current proof-of-concept trial design, but it is not without limitations. This will be the first study to examine the effects of suvorexant during early withdrawal from stimulant use (both cocaine and methamphetamine) in treatment-seeking patients entering residential treatment for StimUD. Furthermore, the well-validated actigraphy-focused sleep assessment will contribute to our understanding of the mechanistic effects of suvorexant in this population. Another first will be leveraging EEG to assess the effects of suvorexant on the waking brain through both resting-state alpha power and the RewP. Finally, this trial will potentially provide effect size estimates of the efficacy of suvorexant regarding the treatment of StimUD, by assessing inpatient treatment completion rates. Despite these strengths, this study will be limited by the open-label design. This could result in the subjective outcomes (eg, sleep quality ratings, stress ratings, and craving scores) being vulnerable to placebo effects, expectancy bias, and demand characteristics. These outcomes will be interpreted cautiously in the statistical analysis. To overcome these concerns, we have included several validated objective outcomes (eg, actigraphy, EEG, and physiological measures), which are less susceptible to participant expectations and will be prioritized when drawing conclusions about treatment effects. Findings from this study will be exploratory and future blinded, placebo-controlled trial designs will establish definitive efficacy.

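### As written, allocation is known before the baseline stress test and EEG on day 1, and plausibly before the baseline self-reports

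*Protocol article*

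**What the plan says.** Study Design states: "We will use an open-label, randomized 2-group design". The Figure 1 legend separates the virtual steps from the in-person ones: "Consent and randomization will occur virtually. Laboratory visits will occur at the Center for Neurobehavioral Research on Addiction". The only virtual contact that Study Design describes is on day 0, when consent, eligibility and baseline actigraphy "will be assessed on day 0 of the study via telephone or video call". Randomization is not in that list.

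The laboratory sessions come next: "On day 1 and day 8, participants will be transported to the outpatient treatment research clinic". At each of them "participants will complete self-report and safety measures (safety measures for the suvorexant group only) followed by administration of the stress reactivity test", and the EEG follows. The abstract's Methods paragraph repeats this for both sessions: "At both study sessions, participants will complete self-report and safety measures (safety measures for the suvorexant group only". Medication covers nights 1 to 7, so the day 1 session is the pre-treatment measurement. The section Safety, Side Effects, and Other restricts the 31-item side-effect questionnaire to the suvorexant group.

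The Statistical Analysis Plan section models each aim 1 and aim 2 outcome on treatment, time and their interaction. The Discussion (Summary) accepts that subjective outcomes risk "being vulnerable to placebo effects, expectancy bias, and demand characteristics", but does not mention the baseline.

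**The concern.** A baseline should be measured before anyone can react to the allocation. Here the stated order puts an arm-specific procedure ahead of two of the baseline measurements. Day 1 is the only pre-treatment session for current stress, craving, drug demand, stress reactivity, resting alpha power and the reward positivity.

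If knowing the arm moves day 1 values differently in the two groups, the interaction can no longer be read as the effect of the drug on change. Disappointment under TAU, or hope under suvorexant, would make the suvorexant baseline look relatively better, and a transient shift of that kind would hide benefit. Over-reporting of symptoms in the suvorexant group would do the opposite. This matters for a trial whose stated purpose is to estimate a plausible range of effects. It also touches measures that the Discussion treats as a safeguard against open-label bias, since HR, BP and cortisol come from a socially evaluated stress test run after allocation is known.

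**Working it through.** **Order of events**

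| Step | What the article gives | What follows |
|---|---|---|
| Randomization | Virtual; day not stated | Could be day 0, or a remote assignment on day 1 |
| Day 1, first block | Self-reports and suvorexant-only safety measures; internal order not given | Staff must know the arm within this block |
| Day 1, next | Stress test, then EEG | Both come after the arm is known |
| Night 1 | First administration, around 10 PM (Intervention) | Day 1 is the pre-treatment value |

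For the stress test and EEG, the stated order settles the matter. For the self-reports it does not, because they share a block with the safety measures; prior knowledge is plausible if randomization takes place at the day 0 contact. No section places disclosure after the day 1 battery.

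**How a shift enters the estimate**

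With two sessions, the interaction is the between-arm difference in (day 8 − day 1). Let knowledge of the arm shift the between-arm difference by s on day 1 and by s′ on day 8. The bias from the baseline shift is −(s − s′). If s′ = s it cancels; if s′ = 0 it enters in full.

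**Scale, from the plan's own figures**

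Inputs from the Statistical Analysis Plan section: 36 analysed (18 per arm assumed), ρ = 0.50, N(0,1) prior on coefficients. Two time points are assumed.

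- SD of change = √(2(1 − 0.50)) = 1. V = 2/18 = 0.111, and SE = √V = 0.333.
- Final effect giving an 80% chance of PP≥75%: 0.674 × √(0.111 × 1.111) + 0.842 × 0.333 = 0.518. Half of that is 0.259, against the stated d = 0.26.
- The same formula at PP≥91% gives 0.752. Half is 0.376, against the stated 0.39.

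The plan's figures are therefore approximately recovered if d is an average over a linear course. On that reading, d = 0.26 corresponds to about 0.52 SD at end of treatment, which is the proper comparator for a bias in change.

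**Illustration with an assumed shift**

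The 0.2 SD shift is an assumption, taken as wholly transient (s′ = 0). PP≥75% is treated as a one-sided test at 0.25, ignoring the weak prior.

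- Unadjusted change, no true effect: 0.2/0.333 = 0.60. Mimicking benefit: P(Z > 0.674 − 0.60) = 47%. Opposite direction: P(Z > 0.674 + 0.60) = 10%. Without a shift: 25%.
- Baseline-adjusted: bias = 0.50 × 0.2 = 0.1; SE = 0.333 × √(1 − 0.50²) = 0.289; 0.1/0.289 = 0.35. The chances are about 37% and 15%.
- True end-of-treatment effect of 0.52 SD with a shift that hides benefit: the chance of PP≥75% falls from 81% to 61%.

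Range for the unadjusted change:

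| Assumed transient shift | Null chance of PP≥75%, shift mimics benefit | Chance of PP≥75% at 0.52 SD, shift hides benefit |
|---|---|---|
| 0 | 25% | 81% |
| 0.1 SD | 35% | 72% |
| 0.2 SD | 47% | 61% |
| 0.3 SD | 59% | 49% |

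**The case against.** The strongest reply is that the timing is inferred. No sentence gives the day of randomization, Figure 1 is not shown, and the Randomization section says that staff see the next assignment only when needed, which fits a release on day 1. The parenthesis about suvorexant-only measures may be loose wording: the Columbia scale is described for each laboratory visit with no arm limit, and nothing says specifically that the 31-item form is used before the first dose. This stands in part. It rules out stating a day 0 randomization as fact, and it leaves the order against the self-reports open. It does not remove the point, because the abstract and Study Design both place the arm-specific measures at the pre-medication session, ahead of the stress test and EEG.

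Second, exposure is uneven, and this stands. Actigraphy takes its baseline from night 0, and whether that follows allocation is unsettled. Aim 3 is modelled on treatment alone. ISI and PROMIS-SF look back 7 days, mostly before any allocation. Stress reactivity is measured before and after the cold pressor within a session, so a constant mood shift drops out. EEG is probably less sensitive to expectancy than self-reports are.

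Third, knowledge of the arm persists in an open-label trial, so a shift equal at both sessions cancels. This also stands: only the part that differs between day 1 and day 8 biases the interaction.

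Fourth, the article already acknowledges open-label bias, says objective measures will be prioritized and calls its findings exploratory. That tempers the weight of the point, but the acknowledgement concerns subjective outcomes in general, and a baseline recorded after disclosure is an avoidable addition.

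**Conclusion.** The point holds in a limited form. As written, allocation is known to staff, and probably to participants, before the baseline stress test and EEG, and plausibly before the baseline self-reports. A shift in day 1 values that does not persist equally to day 8 would bias the treatment × time estimate for outcomes with a day 1 baseline.

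The documents give neither size nor direction. The 0.2 SD illustration rests on an assumed, wholly transient shift, 18 per arm and ρ = 0.50; a shift of that size would be about 38% of the 0.52 SD end-of-treatment effect (0.2/0.52).

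A reader might infer that every baseline in the trial follows open allocation, that a 0.2 SD bias should be set directly against d = 0.26, or that participants will leave on learning their arm before giving any day 1 data. The documents support none of these. Night 0 actigraphy and aim 3 do not rest on the day 1 session, d = 0.26 is described as an average effect, and withdrawal before baseline is only a possibility. This is a worthwhile and inexpensive improvement to the design, not a flaw that invalidates the trial.

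**What to change.** Keep virtual consent on day 0. Release the REDCap assignment only once the day 1 battery is complete and before the first evening administration, and say so in the protocol. Run identical procedures in both arms on day 1, with the safety questionnaire given at that session to everyone or to no one. If this is already the practice, correct the wording in the abstract and Study Design.

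Flag participants randomized before their baseline, keep them in the intention-to-treat analysis, and report an analysis without them only as a supplementary sensitivity analysis. With 8 of 40 enrolled at submission, most of the sample could still benefit.

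The cost is a short amendment, tighter logistics on day 1 and same-evening communication of the assignment to the residential nurses. The treatment schedule does not change.

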**Figure 1. F1:**
[figure not shown]
Study flow diagram. Consent and randomization will occur virtually. Laboratory visits will occur at the Center for Neurobehavioral Research on Addiction. All other activities will occur at the inpatient facilities. NSF: National Sleep Foundation; TAU: treatment as usual.

### Recruitment

Participants will be recruited directly from 2 local inpatient residential treatment facilities in the greater Houston area (The Right Step Houston and Cenikor), both of which provide similar therapeutic programming and services. Patients meeting the preliminary eligibility criteria will be referred to the CNRA by the residential programs. Additional recruitment will include online advertisements and outreach through the University of Texas Health Science Center at Houston (UTHealth Houston), Department of Psychiatry Recruitment Registry. Individuals recruited from outside the residential programs must voluntarily seek admission to one of the residential facilities before participating. Eligibility will be assessed using residential intake records (including a history and physical or psychological assessment) and a phone-based screening. Eligible candidates will participate in a phone interview including the consent process and administration of the structured clinical interview for *Diagnostic and Statistical Manual of Mental Disorders, Fifth Edition* (*DSM-5*) [8] by trained CNRA staff (ie, licensed professional counselor, doctoral student, or postdoctoral fellow). The principal investigator (PI; author HW) and the medical director (author MW) will review intake and phone-interview information to determine final participant eligibility.

### Participants

Participants will be eligible for the study if they are aged between 18 and 65 years and meet the *DSM-5* criteria for a primary StimUD, specifically related to cocaine or methamphetamine. All participants must be fluent in English and capable of fully understanding and providing informed consent for study procedures. These inclusion criteria ensure that participants have the condition of interest and can engage meaningfully with study requirements.

Participants will be excluded if they meet any of the following criteria: (1) diagnosis of an opioid use disorder of any severity; (2) diagnosis of greater than moderate substance use disorder for any substance other than cocaine or methamphetamine; (3) currently receiving medication treatment for withdrawal from any substance; (4) presence of medical conditions that contraindicate the use of suvorexant (eg, severe pulmonary disease, severe cardiovascular disease or clinically abnormal electrocardiogram, severe liver or kidney disease, or sleep disorder—particularly narcolepsy); (5) use of medications known to interact with suvorexant (eg, monoamine oxidase inhibitors, anticonvulsants, haloperidol, phenothiazines, anesthetics, and any sedative); (6) pregnancy or breastfeeding; (7) BMI >30 kg/m^2^ (women only); (8) current *DSM-5* psychiatric disorder or neurological disease requiring ongoing treatment that would make participation unsafe; (9) history of seizure disorder; and (10) history of head injury with loss of consciousness within the past 5 years.

### Randomization

Participants will be randomly assigned in a 1:1 allocation ratio to each treatment group using block randomization. Allocation will use permuted blocks with randomly varying per-arm sizes to minimize predictability while preserving balance. The randomization sequence will be generated in the R Statistical Computing Environment (R Foundation for Statistical Computing) via the blockrand package [9]. A blinded code will be provided to an unblinded study team member who will execute the script, export the allocation file, and upload it to the project’s randomization module in REDCap (Research Electronic Data Capture). The full table will be access restricted such that staff members will see only the next assignment when needed. A read-only copy will be kept safe on a secure drive for emergency unblinding.

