### Intervention

Suvorexant is a dual orexin receptor antagonist approved by the FDA for the treatment of insomnia. In this study, we will administer 10 mg of suvorexant for 7 nights. Two prior studies from our group suggested that suvorexant could be safely administered to individuals with cocaine use disorder [4] and methamphetamine use disorder [10]. The half-life is about 12 hours on average, and steady-state plasma concentrations occur in 3 days with daily administration [11]. A nurse at the residential programs will administer the medication to participants in the suvorexant group each evening before bedtime, at the same time nightly (around 10 PM), with a medication log to monitor compliance.

All participants will receive TAU, consisting of standard programming from the inpatient facilities, including a combination of individual therapy, group therapy, 12-step meetings, case management, and recreational therapy. Participants in the suvorexant group will receive suvorexant and will be asked to avoid medications listed in the exclusion criteria, including sleep-related medications. Participants in the TAU group will continue their usual medication regimen as prescribed by the inpatient facility staff. A comprehensive list of medications prescribed for each patient will be collected. If possible, statistical analyses will attempt to control for other medication exposure.

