All models will use distribution families and link functions as appropriate for each outcome (eg, dichotomous outcomes: binomial, with logit link). Longitudinal models evaluating change via interaction terms (eg, treatment × time) will be reduced to main effects if change is unsupported, and both models will be reported. Model fit information criteria (Akaike information criterion; leave-one-out information criterion) will be used to select structural components including multilevel (eg, random intercepts and slopes) and nonlinear terms. Analyses will be performed in R [35] via packages lme4 [36], rstan [37], and brms [38]. Potential confounders will be identified empirically [39,40] (ie, associated with both predictor and outcome) and modeled with and without adjustment; models with unchanged inference will favor parsimony. Sample characteristics (eg, sex, age, and education) will be evaluated as potential confounders. Analyses will be run in parallel using frequentist and Bayesian models. Frequentist results yield the probability of the data (or data more extreme) given the null hypothesis, whereas Bayesian results directly yield the probability of an alternative hypothesis [41,42]. Frequentist models will use *α*=.05 with false discovery rate correction for exploratory tests. Bayesian priors will be weakly informative (β*~* N(0,1); sd~ Half-Cauchy(0,1); correlation matrices ~ LKJ(2)). Bayesian models will be evaluated via posterior probability (PP) threshold guidelines in the literature [43,44], suggesting that PP=75% to 90% indicates moderate evidence, PP=91% to 96% indicates strong evidence, and PP=97% or above indicates very strong to extreme evidence. Posterior predictive checking, scale reduction factors (“rhat”), and effective sample size will be used to evaluate Bayesian assumptions. Evaluation for frequentist models will use graphical evidence and statistical tests. Generalized linear mixed models inherently accommodate outcome values missing at random; other missing values will be handled by imputation or pattern-mixture modeling. Analyses will follow intention-to-treat principles.

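### Facility should be a prespecified model term, above all for aim 3, because the plan's confounder screen will almost never select it in a randomized trial of 40

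*Protocol article*

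**What the plan says.** **Facilities.** The Recruitment section states: "Participants will be recruited directly from 2 local inpatient residential treatment facilities in the greater Houston area". It describes them as alike: "both of which provide similar therapeutic programming and services". The abstract's Methods paragraph speaks of one facility: "A total of 40 participants, recruited from a residential treatment facility, will be randomized (1:1".

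**Allocation.** The Randomization section states: "Participants will be randomly assigned in a 1:1 allocation ratio to each treatment group using block randomization". It adds: "Allocation will use permuted blocks with randomly varying per-arm sizes to minimize predictability while preserving balance". On access it says: "The full table will be access restricted such that staff members will see only the next assignment when needed". No stratification factor is named, and the words single list or unstratified do not appear.

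**Comparator.** The Intervention section states: "Participants in the TAU group will continue their usual medication regimen as prescribed by the inpatient facility staff". The suvorexant arm is asked to avoid sleep-related medication. Each patient's medications will be listed, and the analysis will try to control for them where possible.

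**Aim 3.** The outcomes are length of stay after treatment and completion of the residential programme. Under Study Design, a stay ends by regular discharge at about 30 days or by early departure. Under Statistical Analysis Plan, each aim 3 outcome is modelled on treatment only.

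**Covariates.** The same section states: "Sample characteristics (eg, sex, age, and education) will be evaluated as potential confounders". A confounder must be found empirically to be associated with both predictor and outcome. Models are fitted with and without it, and the simpler model is favoured when inference does not change. Facility is neither named nor excluded.

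**The concern.** Facility is a known design factor with a plausible link to outcome. Its staff set the control medication, which may include sleep medication, and the aim 3 outcomes are events of the facility's own programme. Such a factor is normally put in the model because of the design. Here it enters only if the data pass a two-sided screen, and it can be dropped again under the parsimony rule.

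One half of that screen asks for association with the predictor, which is randomized treatment. Any such association is chance, so the screen selects facility at roughly the rate of its own significance threshold. It misses moderate imbalances. It also ignores a strongly prognostic factor that happens to be balanced, although adjusting for that factor would improve precision.

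The trial exists to give a plausible range of effects, including effect sizes for programme completion. Precision and an uncontaminated point estimate are therefore what it has to deliver.

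**Working it through.** The article gives no figure on facility balance, so there is none to reproduce. The input taken from it is 20 per arm (40 in total). The facility split, the size of any facility effect and the screening threshold are not given; they are assumptions below.

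**1. Chance imbalance if allocation is not stratified.** With K participants from facility A and 20 per arm, the number X of facility A participants in one arm is hypergeometric (40, K, 20). The difference in share is |2X − K|/20.

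| Facility split | ≥20 points | ≥30 points | ≥40 points |
|---|---|---|---|
| 20:20 | 0.343 | 0.113 | 0.026 |
| 12:28 | 0.301 | 0.082 | 0.014 |
| 8:32 | 0.235 | 0.044 | 0.003 |

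Simulating permuted blocks of 2 to 8 with a 20:20 facility split gives 0.30 to 0.31 for ≥20 points, close to the exact 0.343.

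**2. What the screen detects (20:20 split, assumed threshold 0.05).** Chi-square = 40(ad − bc)²/20⁴.
- 13 v 7: 40(169 − 49)²/160,000 = 3.6, p=0.058; Fisher p=0.113. Not selected.
- 14 v 6: 40(196 − 36)²/160,000 = 6.4, p=0.011. Selected.

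So the predictor half of the screen needs a 40-point imbalance, which has probability 0.026. The outcome half must pass too. For a 0.8 SD facility effect, a t test of 20 against 20 has power of about 0.69, so both halves pass in about 0.026 × 0.69 = 0.018, or 2% of trials. With a 12:28 split, 9 v 3 gives chi-square 40(153 − 33)²/134,400 = 4.29, p=0.038, so the predictor half passes with probability 0.082 by chi-square. By Fisher (p=0.082 at 9 v 3) it needs 10 v 2, with probability 0.014. A looser threshold would select facility more often.

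**3. Shift in one trial.** Shift = imbalance × facility effect.
- Continuous outcome, 20-point imbalance: 0.04, 0.10 and 0.16 SD for facility effects of 0.2, 0.5 and 0.8 SD.
- Completion, assumed 30-point gap between facilities: 0.20 × 0.30 = 6 points; 0.30 × 0.30 = 9 points. For scale, the standard error of a completion difference near 50% is √(2 × 0.25/20) = 0.158, so 9 points is 0.09/0.158 = 0.57 standard errors.

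**4. Long-run behaviour.** Simulation of a single continuous measure with no treatment effect, 20:20 facility split, 12,000 runs per row, two-sided test at 0.05:

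| Facility effect (SD) | Type I, unadjusted | Same, imbalance ≥20 points | Type I, adjusted | SD of estimate, unadjusted | SD of estimate, adjusted |
|---|---|---|---|---|---|
| 0.5 | 5.1% | 6.0% | 5.3% | 0.329 | 0.324 |
| 0.8 | 4.9% | 7.5% | 4.9% | 0.342 | 0.321 |
| 1.0 | 4.6% | 7.7% | 5.0% | 0.354 | 0.323 |

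With no facility effect, the unadjusted type I error is 5.2%, and the SD is 0.317 unadjusted and 0.323 adjusted. Mean unadjusted estimates lie between −0.008 and −0.001 SD throughout, so there is no bias on average.

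In variance terms, adjustment at 0.8 SD gains 0.342²/0.321² = 1.135, equivalent to about 13% more participants. With no facility effect it loses 1 − 0.317²/0.323² = 0.037, about 4%.

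**5. Which aims are exposed.** In aims 1 and 2 the tested term is treatment by time, so a constant facility difference in level cancels. A facility difference in change over time does not. The cancellation is also lost when the model is reduced to main effects, which the plan allows. Aim 3 has no baseline and no such protection.

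**The case against.** The strongest case against runs as follows. Facility is fixed before randomization, so there is no systematic confounding. Chance imbalance is already part of the standard error, and overall type I error stays near 5%. The facilities are described as similar in programming and services. The medication route is addressed by the plan to control for other medication where possible. The covariate list is open. The trial is declared exploratory. The article condenses a fuller protocol, so silence on stratification proves nothing.

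Most of this stands, and it limits the point. A reader might infer three stronger things that the documents do not support:
- **That allocation is one unstratified list.** The reference to a full table fits that reading, but it fits a stratified table too.
- **That facility staff control discharge and do so differently.** Study Design gives one description for all participants, and its examples of early departure are a patient-directed discharge and leaving against advice.
- **That a facility effect would be systematically mistaken for a drug effect.** Randomization rules this out on average.

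What the objection does not remove is the selection rule, which the article does state. An open list helps little when admission depends on a chance association with randomized treatment. The medication adjustment is conditional and covers one route only. Similar programming does not establish equal prescribing or equal completion. A valid unconditional error rate is also no reason to forgo the precision that a known design factor can give.

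**Conclusion.** The point holds as a cheap improvement to the analysis; it is not a validity failure. The stated screen is a poor way to decide on facility. At an assumed 0.05 threshold and a 50:50 split it would include facility in about 2% of trials even if the facilities differed by 0.8 SD. If allocation is not stratified, an imbalance of 20 points or more has probability 0.34 at a 50:50 split and 0.24 at 20:80.

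The consequence is modest. Conditional type I error reaches 7.7% at most in the imbalanced allocations, and that takes an assumed 1.0 SD facility effect. The completion difference shifts by 6 to 9 points under an assumed 30-point facility gap. About 13% in efficiency is forgone at 0.8 SD. Aim 3 is the main exposure; aims 1 and 2 are affected through facility differences in change over time. All these sizes rest on assumed splits and facility effects, and the facilities may in truth differ little. The mismatch between one facility and two in the article is clerical.

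**What to change.** State that facility enters as a prespecified fixed effect, above all in the aim 3 models and also in aims 1 and 2, regardless of the empirical screen and the parsimony rule. In aims 1 and 2 a facility main effect handles level differences only; removing facility differences in change needs a facility-by-time term as well.

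Cost: one degree of freedom per model (one more if facility by linear time is added), and about 4% in efficiency if the facilities do not differ. With a logit link, the adjusted odds ratio for completion is conditional on facility, so report the difference in completion proportions beside it.

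State whether allocation is stratified by facility. If it is not, stratifying the remaining assignments (40 − 8 = 32 when the manuscript was submitted) is optional. It would require regenerating the unused part of the list and could leave overall arm sizes uneven by a participant or two; the model term does most of the work without it. Correct the abstract to two facilities.
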